#### Missing data

We will report the number and percent of missing data for every study variable. We will investigate variables that have relatively high levels of missing data (over 5%) and seek to identify the cause of the missing data and the potential for bias.

#### Interim analysis

There is no planned interim analysis nor any stopping rules.

#### Planned subgroup and adjusted analysis

There are three planned subgroup or adjusted analyses:
The per protocol analysis.Sensitivity analysis for missing data.Separate analyses according to age cohorts (younger - under 75) and (older - 75 and over).

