### Study population

#### Patient inclusion criteria

Patients will be included if they:
Have had NAFLD diagnosed or suspected by their GP.Are aged 18 years or over.Understand the consent procedures and give their full consent.Consent to access of their data from Queensland Health and Medicare Benefits Schedule (MBS) and Pharmaceutical Benefits Scheme (PBS).

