#### Study questionnaire

The study recruitment questionnaire will contain:
Year of birth for calculating age.Gender.Height and weight for calculating BMI.Alcohol consumption in the past year using the 10-item screening tool, Alcohol Use Disorders Identification Test (AUDIT) [13].Current employment status for the economic analysis.EQ-5D-3 L [14] for estimation of health-related quality of life for the economic analysis.

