### Statistical analysis

#### Sample size and statistical power

We have a minimum total sample size of 156 participants for our primary outcome of time to diagnosis, but we will aim for a sample size of 234. Two hundred and 34 participants will give us a 95% power to detect a 50% reduction in the primary outcome of time to diagnosis of high-risk disease. Our lower sample size of 156 gives us an 83% power. We used a two-sided 5% significance level. We assumed an average diagnosis time of 180 days in the usual care group, and a halving of this time in the intervention group. We assumed that 5% of participants would be censored due to death or loss to follow-up. The sample size was estimated by simulating survival data using the “sim.survdata” function from the “coxed” package in *R* using 1000 simulations [16]. We assumed a log-normal hazard function with a standard deviation of 10 days. The statistical code to run the sample size is available here: https://github.com/[name]/LOCATE. We assume that half of all patients approached will agree to participate, hence, we aim to approach 468 people.

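### Separate analyses under 75 and at 75 or over give no estimate of how the effect differs by age, and the older group's primary result is likely to be very imprecise

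*Protocol article*

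**What the plan says.** Under *Planned subgroup and adjusted analysis* the protocol article lists three items: the per protocol analysis, a sensitivity analysis for missing data, and "Separate analyses according to age cohorts (younger - under 75) and (older - 75 and over"). Only the last is a subgroup question in the usual sense. The item names no interaction term and no comparison of the two age-specific effects. It also does not say which outcomes or models it covers.

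The related facts are these.

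- **Age.** Participants qualify if they "Are aged 18 years or over", with no upper limit (*Patient inclusion criteria*). The recruitment questionnaire records "Year of birth for calculating age" (*Study questionnaire*). No expected age distribution is given.
- **Size.** "We have a minimum total sample size of 156 participants for our primary outcome of time to diagnosis, but we will aim for a sample" of 234 (*Sample size and statistical power*). The power statement covers the overall comparison only.
- **Primary event.** It is a diagnosis of clinically significant fibrosis, with transient elastography above 8.0 kPa (*Primary clinical outcome*), so low-risk participants cannot have it. It is analysed with Weibull survival models.
- **Randomisation.** It is stratified by health service, not by age.

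**The concern.** Whether the model of care works differently in older patients is a question about the difference between two effects. Separate analyses estimate each effect and leave the reader to compare them by eye. When one group is much larger than the other, the usual result is an interval that excludes no effect in the large group and one that includes it in the small group. That pattern arises even when the true effects are identical, yet it is easily read as evidence that the service fails in the small group.

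The cut at 75 makes such an imbalance likely. Recruitment starts at age 18, and advanced cardiac disease and terminal illness are excluded, which tends to thin the oldest group. The results go to health services and policy makers, so an unsupported statement about older patients could affect who is offered the service.

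**Working it through.** **Part 1: what separate fits can show.** This needs no figures. If b_old and b_young are the two log hazard ratios, the age question concerns b_old − b_young, with variance Var(b_old) + Var(b_young). Neither separate fit reports that quantity or its interval. A treatment-by-age interaction in one model does.

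**Part 2: the plan's own power figure.** The plan states that 234 "participants will give us a 95% power to detect a 50% reduction in the primary outcome of time to diagnosis of high-risk disease" and that "Our lower sample size of 156 gives us an 83% power". Its inputs are "We assumed an average diagnosis time of 180 days in the usual care group, and a halving of this time in the intervention group", 5% censoring, and "We used a two-sided 5% significance level". With exponential times, halving the mean gives a hazard ratio (HR) of 0.5. The Schoenfeld approximation is power = Φ(|ln HR| × √events / 2 − 1.96).

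- 234 × 0.95 = 222 events: 99.9%
- 156 × 0.95 = 148 events: 98.8%

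This does not reproduce 95% and 83%. The plan's figures came from simulation with a different event-time model, and the code is not in the article, so the mismatch does not show them to be wrong. Nothing below depends on it.

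**Part 3: events in the older group.**

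Inputs:
- N = 234 (target) or 156 (minimum), from the protocol article.
- 95% uncensored, from the protocol article.
- Share aged 75 or over: not given; *assumed* 5-20%.
- Share high-risk: *assumed* 10-40%. *Background* says that 60-90% of NAFLD patients do not have advanced fibrosis; the complement serves as a proxy for exceeding 8.0 kPa. The 17% column is the top of the 12-17% range that *Background* gives for primary care patients with NAFLD and type 2 diabetes.

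Events = N × share 75+ × share high-risk × 0.95. For example, 234 × 0.10 × 0.40 × 0.95 = 8.9.

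| Share 75+ | Participants 75+ | 10% high-risk | 17% | 40% |
|---|---|---|---|---|
| 5% | 11.7 | 1.1 | 1.9 | 4.4 |
| 10% | 23.4 | 2.2 | 3.8 | 8.9 |
| 15% | 35.1 | 3.3 | 5.7 | 13.3 |
| 20% | 46.8 | 4.4 | 7.6 | 17.8 |

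At N = 156 every count is one third lower.

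**Part 4: precision and power within the older group.** The standard error of the log HR is about 2/√events, so the 95% interval is the estimate multiplied and divided by exp(1.96 × 2/√events).

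- 8.9 events: factor 3.7, power for HR 0.5 about 18%. The younger group would have 80 events, factor 1.55, power 87%.
- 17.8 events: factor 2.5, power 31%.
- 1.1 events: power about 6%; the interval is uninformative.

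At 80% power HR 0.5 needs 66 events. At 40% high-risk that means 66 / (234 × 0.40 × 0.95) = 74% of the sample aged 75 or over.

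**Part 5: estimability.** An arm with no events gives no finite hazard ratio. The chance that both arms have at least one is [1 − (1−p)^n1] × [1 − (1−p)^n2], ignoring the 5% censoring.

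| Participants 75+ (arms) | p = 10% | p = 12% | p = 17% | p = 40% |
|---|---|---|---|---|
| 12 (6/6) | 22% | 29% | 45% | 91% |
| 23 (11/12) | 49% | 59% | 78% | 99% |

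Failure to fit is therefore a real possibility when both shares are low, and unlikely when 40% are high-risk.

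**Part 6: power of the interaction.** SE = √(4/events_old + 4/events_young). For HR 0.5 in one age group and 1.0 in the other, power = Φ(ln 2 / SE − 1.96). With 8.9 and 80.0 events, SE = √(0.449 + 0.050) = 0.71 and power is about 16%. Over the Part 3 grid at N = 234 it runs from about 5% to 26%. These figures treat age as two groups.

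**The case against.** The strongest case against has four parts.

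- **Sparsity is not documented.** A reader might infer that the older group is certain to have only a handful of events and that its Weibull model will often fail. The article does not support this. It gives no age distribution, and the 12-17% figure describes primary care patients with type 2 diabetes, whereas participants here are referred to hepatology clinics with or without diabetes. At a 15-20% older share with 40% high-risk, 13 to 18 events are expected. If 95% of all participants had the event, as the sample-size assumption implies, a 10% share gives 234 × 0.10 × 0.95 = 22 events. This objection stands, so the sparsity claim must be conditional. Even 22 events give only about 37% power.
- **The item is not confined to the primary outcome.** Time to first Fibroscan assessment and quality of life do not depend on being high-risk and would give imprecise but usable results in about 23 older participants. This also stands. The event counts bear on the primary outcome only; the lack of a comparison between age groups applies to every outcome.
- **The purpose may be descriptive, and the interaction may sit in an analysis plan not shown.** The article never says that it will test effect modification, and it favours confidence intervals over p-values in external papers. That reduces the risk of misreading but does not remove it, since two intervals of unequal width invite the same contrast. The article also does more than stay silent: it fixes separate analyses and the cut.
- **The remedy has little power.** This is true, and it is why the interaction should be labelled exploratory. Its gain is that it estimates the right quantity and shows the uncertainty in it.

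**Conclusion.** The point holds in a limited form. As worded, the age analysis yields two effects and no estimate of their difference; this follows from the text alone and needs no assumption.

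The older group's primary result is likely to be very imprecise: about 1 to 9 events at N = 234 if 5-10% are aged 75 or over and 10-40% are high-risk, and up to about 18 at a 20% share. Both ranges are assumptions. The high-risk range is a proxy, and the share above 8.0 kPa could be higher or could rise with age. The power figures use the Schoenfeld approximation, which is optimistic if low-risk participants stay in the risk set without being able to have the event. Failure to fit is a possibility at the low end, not an expectation throughout.

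This is a minor, inexpensive improvement to a secondary analysis. It does not affect the primary comparison.

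**What to change.** Replace the separate fits, or accompany them, with one model in all participants that contains treatment, age and their interaction. Age is preferably continuous, calculated from year of birth. Then:

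- report the interaction estimate with its 95% confidence interval, and label it exploratory with low power;
- base any statement about a difference by age on that estimate alone;
- where events at 75 or over are too few to fit a model, give descriptive counts by arm for that group.

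The cost is a few sentences of analysis wording and no new data. The downside is that a continuous-age interaction assumes a smooth, for example linear, change of effect with age, which sparse data at the oldest ages can check only weakly. Continuous age is a preference; an interaction with the planned two age groups would also supply the missing comparison, with the low power shown above.

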#### Additional information

The results will be written up using the Consolidated Standards of Reporting Trials (CONSORT) and Template for Intervention Description and Replication (TIDieR) checklists [21, 22]. As per the CONSORT guidelines, we will not use statistical tests to compare the two groups of patients at baseline and will instead look for differences using a table of summary statistics.

## Discussion

### Dissemination of results

Results will be directly disseminated to each participating health service using a report that will include:
A brief lay summary of the results in their health service.The detailed overall results.

At recruitment all participants will be asked if they would like to receive a summary of the results, and those who agree will be emailed a one-page lay summary once the analyses have been written up.

#### Dissemination of results to health consumers, policy makers and other stakeholders

Results will be directly disseminated to key staff in Queensland Health for further distribution to consumers, policy- and decision-makers in the form of evidence briefs, plain language summaries and policy recommendations. A publication plan that details the likely papers and conferences will be established to inform systematic publication of results through the clinical and academic communities. We will adhere to the International Committee of Medical Journal Editors requirements for authorship and will report the contributions of each author. We will not use professional writers. The protocol will be publicly available via ANZCTR (https://www.anzctr.org.au) – trial number ACTRN12620000158965. This is a nationally important health services research trial that examines a change to the model of care for triaging patients with liver disease. A relatively simple change to care could result in earlier identification of patients with significant liver disease and lower overall costs for the health system. The study uses a strong randomised design and will collect high quality data to provide clear information for decision-makers. The implementation component of the study will provide valuable information for other health services that may want to implement the model of care based on the trial results.

## Data Availability

The datasets generated and/or analysed during the current study are available in the *github* repository (https://github.com/[name]/LOCATE).

## Abbreviations

LOCATE-NAFLD: LOCal Assessment and Triage Evaluation of Non-Alcoholic Fatty Liver Disease
LOCATE: LOCal Assessment and Triage Evaluation
NAFLD: Non-alcoholic fatty liver disease
HHSs: Hospital and Health Services
ANZCTR: Australian New Zealand Clinical Trials Registry
MBS: Medicare Benefits Schedule
PBS: Pharmaceutical Benefits Scheme
CONSORT: Consolidated Standards of Reporting Trials
TIDieR: Template for Intervention Description and Replication
HCC: Hepatocellular Carcinoma
GP(s): General Practitioner(s)
BMI: Body Mass Index
AST: Aspartate aminotransferase
ALT: Alanine transaminase
AUDIT: Alcohol Use Disorders Identification Test
TE: Transient Elastography
HREC: Human Research Ethics Committee
SMS: Short Messaging Service
